# HRV-Guided Training for Elders after Stroke: A Protocol for a Cluster-Randomized Controlled Trial

**DOI:** 10.3390/ijerph191710868

**Published:** 2022-08-31

**Keywords:** heart rate variability, HIIT, cardiac rehabilitation, safety, adherence, VO_2peak_, protocol

## Abstract

There are many consequences associated with having a stroke, all of which are important factors affecting long-term rehabilitation outcomes; these become important health issues for those of advanced age and require dedicated health strategies. High-intensity interval training (HIIT) is an effective training protocol used in cardiac rehabilitation programs; however, owing to the inter-individual variability in physiological responses to training associated with cardiovascular diseases, the exercise regimen given to each patient should be closely controlled and individualized to ensure the safety and efficiency of the exercise program. Heart rate variability (HRV) is currently being used for this purpose, as it is closely linked to parasympathetic nervous system activation, with high HRV scores associated with good cardiovascular adaptation. The objective of this protocol is to determine the effect of HIIT compared to HRV-guided training in terms of cardiorespiratory fitness, heart rate variability, functional parameters, body composition, quality of life, inflammatory markers, and cognitive function in patients who have had a stroke, as well as to assess the feasibility of patients undertaking an 8-week cardiac rehabilitation program, evaluating its safety and their adherence. The proposed protocol involved cluster-randomized controlled design in which the post-stroke patients are assigned either to an HRV-based training group (HRV-G) or a HIIT-based training group (HIIT-G). HIIT-G will train according to a predefined training program, whereas HRV-G will train depending on the patients’ daily HRV. The outcomes considered are peak oxygen uptake (VO_2peak_), endothelial and work parameters, heart rate variability, functional parameters, relative weight and body fat distribution, quality of life, inflammatory markers and cognitive function, as well as exercise adherence, feasibility, and safety. It is expected that this HRV-guided training protocol will improve functional performance in patients following a stroke and be safer, more feasible, and generate improved adherence relative to HIIT, providing an improved strategy for to optimize cardiac rehabilitation interventions.

## 1. Introduction

Non-communicable chronic diseases are among the main health problems worldwide. According to the U.S. Department of Health and Human Services, cardiovascular diseases, diabetes mellitus, and obesity account for approximately two-thirds of deaths globally and are responsible for 73.5% of total deaths [1]. Individuals tend to accumulate coexisting diseases as they age. With advanced age, patients with risk factors for atherosclerosis would be expected to show multiple cardiac, aortic, extracranial, intracranial, and penetrating artery occlusive lesions that pose a stroke risk [2]. Therefore, it is not surprising that 88% of subjects with a first diagnosis of chronic heart disease are aged between 65 and 80 years [3], making this a common pathology among older people.

A stroke is a cardiovascular disease that affects the blood vessels supplying blood to the brain [4], resulting in nerve cell death in the affected brain tissue [5]; therefore, strokes are also known as brain infarcts, a heterogeneous disease with more than 150 known causes that can be categorized as ischemic or hemorrhagic strokes, subarachnoid hemorrhages, cerebral venous thrombosis, or spinal cord strokes [6]. The pathophysiological processes involved after a stroke include bioenergetic failure, acidosis, loss of cell homeostasis, excitotoxicity, and disruption of the blood–brain barrier [5], generating an inflammatory process. According to Pecherstorfer et al. (2009) [4], the consequences of a stroke are manifold, depending on the location of the affected brain regions, and can involve physical, cognitive, emotional, sexual, and vocational impairment, as well as social handicap. All of these are important factors affecting long-term rehabilitation outcomes and become important health issues for those of advanced age, requiring dedicated health strategies.

One such strategy is physical exercise, which has become an important tool in cardiac rehabilitation programs. Taylor et al. (2004) [7], in a systematic review with meta-analysis, pointed out that the physical training included in cardiac rehabilitation programs is associated with a reduction of 26% in the patient mortality rate. More recently, in another systematic review with meta-analysis, Kraus et al. (2019) [8] determined that low volumes of exercise were enough to produce health benefits in cardiovascular disease patients and that vigorous physical exercise reduced the mortality risk by 75% in this population. In this regard, it is well established that high-intensity interval training (HIIT) is an efficient and safe training protocol for improving VO_2_ [9] and other physical and physiological parameters [10], reducing the risk of cardiovascular diseases.

On the other hand, the anti-inflammatory response after HIIT has been investigated in middle-aged and older people, with no consensus reached between studies. According to the two systematic reviews with meta-analysis mentioned above, resistance training has a positive effect on anti-inflammatory biomarkers [11], whereas the effect of HIIT is still unclear [12]. Moreover, it is essential to evaluate hippocampal functionality in order to determine the cognitive effects of improved cardiac functions and improved cognition associated with the practice of physical exercise with aging [13]. Therefore, it would be interesting to determine whether different training regimes generate different cognitive adaptations following a stroke.

However, cardiac rehabilitation is often carried out in groups, and it is recognized that group training using the same standardized training program can result in a wide range of reactions in terms of performance and physiological adaptations [14,15]. Given that an individual’s cardiovascular system can be affected by a stroke to varying degrees, the exercise regime given to each patient should be closely controlled and individualized, thus avoiding overstimulation of the cardiovascular system during training while increasing safety and efficiency. However, serious adverse events still occur in cardiac rehabilitation during HIIT or moderate-intensity training [16]. As stated by Schmitt et al. (2018) [17], an important component of the interindividual variability in the physiological responses to training is related to the balance between the parasympathetic (PNS) and sympathetic (SNS) activity of the autonomic nervous system (ANS). In this regard, heart rate variability (HRV) is currently used as an indicator of the physical and psychological state of athletes, enabling coaches and scientists to individualize training.

HRV is defined as the fluctuation in the interval between consecutive heartbeats and the fluctuation between consecutive instantaneous heart rates [18]. Therefore, it is linked to the functioning of the autonomic nervous system and the fluctuation between sympathetic and parasympathetic activation. Healthy subjects are usually characterized by a predominantly parasympathetic system at rest, involving a low heart rate and high HRV and demonstrating improved cardiovascular system adaptation and a positive state of health [19]. In contrast, cardiovascular diseases, such as hypertension, ventricular arrhythmia, chronic heart failure, or ischemic heart disease, increase the predominance of the sympathetic system, which is reflected in a high resting heart rate and low HRV [20,21,22]. According to the New York Heart Association, there is a strong correlation between low scores in HRV temporal parameters and mortality after a stroke [23]. Moreover, Daminello et al. (2013) [24] concluded that in stroke patients, during exercise, HRV decreases and does not return to baseline within the first 30 min after exercise. Thus, they considered HRV an important method for appropriate prescription of exercise for this group of patients.

HRV can be used not only to detect cardiovascular disease severity but also to reflect a reduction in disease impact. This means that HRV can be used in any therapy that aims to shift the autonomic equilibrium toward parasympathetic dominance and a reduction in the sympathetic tone [25], with the objective of increasing homeostasis of the autonomic nervous system. To this end, training should focus on cardiovascular system adaptability. In this regard, HRV biofeedback has achieved positive results by maximizing the heart rate increment during inspiration and reducing it during exhalation by means of various breathing techniques [26,27]. Similarly, Nishime et al. (2000) [28] reported that recovery after an exercise test serves as a good indicator of cardiac disease rehabilitation, as better recovery indicates a lower mortality rate. According to López-Chicharro et al. (2013) [29] and Hackney et al. (2006) [30], training at moderate-to-high intensity is related to a reduction in sympathetic activation. Moreover, a recent systematic review with meta-analysis revealed that basal HRV can increase following HIIT training [31].

Therefore, HRV is a biomarker that can indicate the health status of the cardiovascular system, serving as an effective tool for individualizing the training load in cardiac patients. Moreover, it can be used to measure cardiovascular responses to therapeutic interventions, with HIIT-based exercise being the most recommended option. However, with the goal of obtaining improved results regarding cardiovascular rehabilitation, it is still unclear whether to opt for HIIT training or to individualize HIIT training using HRV. We hypothesize that (i) both HIIT training and HRV-guided training will improve cardiorespiratory fitness, functional performance, heart rate variability, relative weight and fat distribution, inflammatory markers, cognitive function, and quality of life in post-stroke patients but that HRV-guided training will achieve better results; and (ii) HRV-guided training will be safer and more feasible and will generate more patient adherence to the program. The primary objective of the proposed protocol is to determine the effect of HIIT- compared to HRV-guided training on cardiorespiratory fitness in post-stroke patients who undertake an 8-week cardiac rehabilitation program. The secondary aims of this trial are (i) to determine the effect of HIIT training compared to HRV-guided training on heart rate variability scores in post-stroke patients, (ii) to investigate the effect of each exercise program in terms of the adaptations obtained in functional parameters, body composition, and the quality of life of these patients, (iii) to study the effect of both programs on inflammatory markers, (iv) to determine which exercise program is more effective at improving cognitive function, and (v) to analyze whether the two exercise programs are equally feasible and safe, as well as to evaluate their effect on patient adherence to the cardiac rehabilitation program.

This will be an 8-week, single-center, prospective, cluster-randomized controlled trial protocol in which post-stroke patients are assigned to either an HRV-based training group (HRV-G) or a HIIT training group (HIIT-G). A block randomization method will be used to randomly assign groups to interventions in equally sized sample groups. This protocol was designed in accordance with the Standard Protocol Items: Recommendations for Interventional Trials (SPIRIT) Statement [32]. To describe the intervention, the TIDieR (Template for Intervention Description and Replication) checklist by Hoffmann et al. (2014) [33] was used.

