### 2.7. Allocation and Blinding

A block randomization method will be used to allocate participants to the groups, which will contain equal sample sizes. Blocks will be chosen randomly by tossing a coin to determine participant assignment to the groups. This procedure will be carried out by the data monitoring committee. The participants and the data monitoring committee will be blinded to the group assignment exercise.

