### 2.8. Data Analysis

The data monitoring committee will have full access to the complete final dataset. The data will be analyzed using Jamovi (Jamovi Project 2018, version 0.9.1.7, Jamovi, Sydney, Australia) and RStudio 3.15.0 software. Prior to data analysis, the Kolmogorov–Smirnov test and the Levene test will be performed to determine the normal distribution of the variables and the homogeneity of variance. For a variable to be considered as having a normal distribution, 95% of values will have to be within two standard deviations of the mean. Descriptive data will be reported as mean ± SD and range. All data will be analyzed based on the intention-to-treat principle (the last observation carried forward). If the sample is normally distributed, the Student’s *t*-test for independent samples will be used to compare the two intervention groups for the pretest, whereas ANCOVA will be used for the post-test, using the basal scores and age as covariables. Moreover, the Student’s *t*-test for related samples will be calculated to compare variables before and after the intervention in each group. If the sample is non-parametric, Kruskal–Wallis and the Mann–Whitney U tests will be used, respectively. The standardized mean differences (Cohen’s effect size) will be calculated together with the 95% confidence intervals [56]. The effect sizes (ESs) will be calculated using Cohen’s d (Hopkins). The relationship between variables will be assessed using the Pearson r correlation coefficient. If r is higher than 0.7, the determination coefficient (r^2^) will be used to determine the percentage of Y variation with regard to the X variation. Significance will be accepted at *p* ≤ 0.05.

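### The plan does not settle whether patients or groups are randomised, while its sample size and tests are valid only for individually randomised patients

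*Protocol article*

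**What the plan says.** The design label appears three times in the Protocol article. The title reads "A Protocol for a Cluster-Randomized Controlled Trial". The abstract has "The proposed protocol involved cluster-randomized controlled design in which the post-stroke patients are assigned either to an HRV-based training group". The design paragraph closing Section 1 has "This will be an 8-week, single-center, prospective, cluster-randomized controlled trial protocol". One sentence there goes beyond the label and names groups as what is assigned: "A block randomization method will be used to randomly assign groups to interventions in equally sized sample groups".

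Section 2.7 names participants: "A block randomization method will be used to allocate participants to the groups, which will contain equal sample sizes". It then gives the mechanism: "Blocks will be chosen randomly by tossing a coin to determine participant assignment to the groups".

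Section 2.5 sets 30 patients per arm, 60 in all, from an SD of 4.75 mL/kg/min and an error of 1.7, and attaches 97% power. Section 2.8 compares the arms before treatment with an independent-samples t-test, and afterwards "ANCOVA will be used for the post-test, using the basal scores and age as covariables". The fallback is rank tests. None of these methods has a term for clusters.

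**The concern.** The unit of randomisation decides which analysis is valid. If training groups or whole blocks are randomised, patients in the same unit may have correlated outcomes. A patient-level ANCOVA with no cluster term then understates the standard error of the VO2peak comparison whenever the ICC is above zero: confidence intervals are too narrow, the type I error exceeds 5%, and the stated precision and power are too favourable.

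If individual patients are randomised, the sample size and tests do not suffer from this, but the title, abstract and design paragraph misdescribe the trial. Readers and meta-analysts would then look for, or apply, a clustering correction that does not belong.

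The concern does not rest on the article leaving out an ICC or a cluster count, which a full protocol or analysis plan could supply. It rests on two units being stated, together with a sample size and tests that fit only one of them.

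**Working it through.** **Step 1: the statements side by side.**

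| Place | What is assigned |
|---|---|
| Title | label only: cluster-randomised |
| Abstract | label cluster-randomised, but patients are assigned |
| Section 1, design paragraph, first sentence | label cluster-randomised, but patients are assigned |
| Section 1, design paragraph, second sentence | groups |
| Section 2.7 | participants, through blocks chosen by coin toss |
| Sections 2.5 and 2.8 | patients treated as independent |

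There is one centre, so hospitals cannot be the clusters, and no other cluster is defined.

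**Step 2: reproduce the plan's figures.** From Section 2.5, SD = 4.75, d = 1.7, z = 1.96.

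- n = z² × SD² / d² = 1.96² × 4.75² / 1.7² = 29.99, so 30 per arm. (Section 2.5 prints the ratio the other way up, which gives 0.49; that is a separate matter.)
- Power with 30 per arm, a difference of 1 SD and two-sided 5% (sidedness assumed): 97.2% by the normal approximation, 96.8% by the t distribution. This matches the stated 97%, taking the wording on variance to mean a 1 SD difference.

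Both figures come out with independent patients, that is, with a design effect (DE) of exactly 1.

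**Step 3: the same 60 patients if clusters are randomised.** Cluster size m and the ICC are not in the article. Assumed ranges: m = 5, 10, 15 (6, 3 or 2 clusters per arm) and ICC = 0.01, 0.05, 0.10.

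- DE = 1 + (m − 1) × ICC
- Effective total = 60 / DE
- Type I error of a patient-level test = 2 × (1 − Φ(1.96 / √DE))
- n per arm to keep the information of 30 independent patients = 30 × DE, rounded up
- Power for 1 SD: t test on (clusters − 2) degrees of freedom

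| m | ICC | DE | Effective total | Type I, formula | Type I, simulated | n per arm | Power |
|---|---|---|---|---|---|---|---|
| 5 | 0.01 | 1.04 | 57.7 | 5.5% | 5.5% | 32 | 93% |
| 5 | 0.05 | 1.20 | 50.0 | 7.4% | 7.4% | 36 | 89% |
| 5 | 0.10 | 1.40 | 42.9 | 9.8% | 9.8% | 42 | 84% |
| 10 | 0.01 | 1.09 | 55.0 | 6.0% | 5.7% | 33 | 79% |
| 10 | 0.05 | 1.45 | 41.4 | 10.4% | 10.5% | 44 | 68% |
| 10 | 0.10 | 1.90 | 31.6 | 15.5% | 15.9% | 57 | 57% |
| 15 | 0.01 | 1.14 | 52.6 | 6.6% | 6.7% | 35 | 50% |
| 15 | 0.05 | 1.70 | 35.3 | 13.3% | 13.3% | 51 | 38% |
| 15 | 0.10 | 2.40 | 25.0 | 20.6% | 20.9% | 72 | 30% |

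The simulation used 40,000 null trials per row and a two-sample t-test on 30 against 30 patients. A separate run of the same size gave 21.5% for the last row, hence the upper end of about 22%.

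The standard error is understated by √DE, a factor of 1.02 (√1.04) to 1.55 (√2.40). The planned half-width of 1.7 becomes 1.7 × 1.02 = 1.73 up to 1.7 × 1.55 = 2.63 mL/kg/min.

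**Step 4: one cluster per arm.** Degrees of freedom are 2 − 2 = 0, so no valid cluster-level test exists.

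**The case against.** The best defence is that only the label is wrong. The abstract and the first sentence of the design paragraph both have patients being assigned. The sentence about assigning groups could be loose wording for two arms of equal size. With one centre, no named cluster, and a patient-level sample size and analysis, a mislabelled individually randomised trial is at least as plausible as a misanalysed cluster trial. This stands, and it means that a reader who infers that the p-values and intervals are wrong goes further than the article allows. They are wrong only if clusters are randomised and the ICC is above zero.

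The opposite inference also goes too far. A reader might take Section 2.7 to allocate patients one at a time and conclude that striking the word cluster is the right repair. The section says that the coin chooses blocks. That may mean permuted-block sequences for individuals, or whole blocks of patients sent to one arm, in which case the block is the cluster and dropping the label would hide the true design.

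Two limits on the numbers also stand. The simulation used a t-test, whereas the planned comparison is an ANCOVA on baseline and age; the covariate-adjusted ICC is the relevant one and could be smaller or larger. At ICC 0.01 the inflation is slight. Finally, Section 1 remarks that cardiac rehabilitation is often delivered in groups. If this trial's sessions are shared, some correlation could remain even under individual randomisation, but the remark is general and does not establish that.

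**Conclusion.** The contradiction is in the current text and nothing else in the article resolves it. The 30 per arm, the 97% power and the planned tests hold only for individual randomisation, so either the design description or the sample size and analysis must change. Which of the two cannot be decided from the article.

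If patients are individually randomised, this point leaves the numbers as they are and the fault is one of description. If clusters are randomised, the consequence ranges from slight (type I error of 5.5% to 6.7% at ICC 0.01) to serious (13% to 22% with two clusters of 15 per arm at ICC 0.05 to 0.10). That range rests wholly on assumed cluster sizes and ICCs. The unit has to be resolved before the primary VO2peak comparison is run, because the validity of that test depends on it.

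**What to change.** State the unit that is actually randomised, say what a block is in Section 2.7, and make the title, abstract, design paragraph and Sections 2.5, 2.7 and 2.8 agree.

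- **If individual patients are randomised:** remove the cluster-randomised label and the sentence assigning groups, and keep the ANCOVA. Cost: wording only.
- **If training groups or whole blocks are randomised:** keep the label and define the cluster. Analyse VO2peak with the ANCOVA plus a random group intercept and small-sample degrees of freedom (for example Kenward-Roger), or with a cluster-level test on (clusters − 2) degrees of freedom. Have at least two, and preferably more, clusters per arm. Restate the precision and the 97% power in Section 2.5 with the design effect. Cost: clearly lower stated precision and power at 60 patients. Keeping the information of 30 independent patients per arm would take 32 to 72 per arm over the assumed range. With one cluster per arm, no analysis repairs the design.

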## 2. Materials and Methods

### 2.1. Study Setting

To select a sample with the desired characteristics, University Hospital Torrecárdenas, (Almería, Spain) was chosen as the location to carry out this protocol. The room rate assigned to the cardiology section in this hospital is up to 0.77%, and re-admission as a result of cardiovascular diseases has increased by 64.79% in the past year. Within the internal organization system, two phases of care are considered for patients with cardiovascular events. In phase 1, the patient is attended by a cardiologist, who is responsible for detecting the origin of the event, sending the patient to surgery (if necessary) and prescribing medication. The physical condition level is also determined in phase 1 using a treadmill test (a modified Bruce protocol). Then, patients are invited to participate in phase 2, which consists of an 8-week cardiovascular rehabilitation program. This is conducted by a multidisciplinary group comprising a rehab doctor, a physiotherapist, and a nurse. The proposed protocol will be implemented in phase 2.

